### General objectives

We aim to conduct a Phase I trial to demonstrate the feasibility and safety of non-invasive ventilatory support in cerebral malaria (Blantyre coma scale ≤2) and history of seizures to generate preliminary data on seizure control and neurological status in those surviving to 28 and 180 days.

**
*Specific objectives*
**

**(i)** To initially examine whether it is safe, feasible and practical to implement a protocol for the use of NIV with BCV, with or without the use of Hi-Flow AirVO2 technology (to treat hypercarbia (PCO
_2_))
**(ii)** To implement our refined-protocol for BCV use in cerebral malaria in addition to prophylactic ASM (LVT) to reduce the complications of cerebral malaria.
**(iii)** To estimate the occurrence of adverse events using BCV, including episodes of bradypnoea or apnoea; hypoxaemia (oxygen saturations <92%); number of episodes of hypercarbia (pCo2>45mmHg since this will worse brain swelling), and number of aspiration events (given that all children will routinely having nasogastric tubes and regular suction)

**Site:** High dependency ward in Kilifi County Hospital, Kenya.

**Study design**: Phase I trial to generate feasibility, safety and preliminary data on seizure control and survival to 28 days of non-invasive ventilatory support and seizure prophylaxis in cerebral malaria.

**Study Population:** 30 children hospitalised with cerebral malaria

**
*Inclusion criteria*
**

1. Aged 3 months and 12 years (up to 40 kg in weight for paediatric dosing of LVT) admitted to the paediatric ward.2. Current or recent evidence of
*P. falciparum* malaria (slide or rapid diagnostic test (RDT) positive)3. Blantyre Coma Score2 or less that persists even after correction for concurrent hypoglycaemia (defined as glucose <3 mmol)4. History of seizures in this illness5. Guardian or parent willing and able to provide consent

**
*Exclusion criteria*
**

1. Known cerebral palsy or significant neuro-development delay (which will affect endpoint assessment)2. Skin disease or burns preventing use of the BCV3. Respiratory or cardio-respiratory arrest prior to enrolment4. A comorbidity which clinician believes has a significant risk of poor outcome e.g. malignancy, end-stage renal failure, major cardiac condition

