### Sample size determination

This is a Phase I trial designed to test the feasibility, tolerability and safety of using non-invasive ventilatory support in cerebral malaria. We plan to initially enrol 10 children with CM and a history of seizures (see inclusion criteria above) as this selects a high-risk group with ~90% risk of further seizures who will all require first line (diazepam) and many will require second-line (phenobarbitone) anticonvulsants, all with an inherent risk of respiratory depression or aspiration (15% in the control group of the Malawi trial Trials.gov (Trial reference NCT01982812)).

Following this initial phase the next 10 children will receive a neuroprotective strategy of BCV plus LVT 40 mg/kg loading dose and 30mg/kg every 12 hours given via nasogastric tube for 3 days or until coma resolution.

If this reduces seizures that are short lived and are not clinically-relevant (so 80% do not require additional ASM (based on the judgement of an independent Data Monitoring Committee, i.e. that do not require addition ASMs with minimal adverse events), then an additional 10 children will be studied using LVT at this dosage, without dose escalation.

If this fails to adequately control seizures, the neuroprotective strategy of BCV plus a higher dose (150%) of LVT will be studied, namely 60 mg/kg loading dose and 45mg/kg every 12 hours given via nasogastric tube for 3 days or until coma resolution.

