### Secondary endpoints

Feasibility will be assessed by ability to implement/operationalise the BCV for use on the high dependency ward in Kilifi County Hospital (assessed by whether this can generate negative pressure ventilation as per specification by the Hayek recommendations and averts respiratory safety endpoints).

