### Safety endpoints

Aspiration (sudden decrease in oxygen saturations, and/or denovo presence of coarse chest crepitations, with evidence of gastric reflux/aspirate in the oropharynx).

Episodes of hypercarbia (defined as pCO2 level of greater than 45 mmHg).

Episodes of bradypnoea and hypoxaemia (oxygen saturation <92%) in a child with unrousable coma (Blantyre coma scale≤2) (bradypnoea defined as <10, 15 or 20 breaths/minute over 3 minutes for those aged <6m, 6–36m and >36m respectively).

Development of hypotension (defined as systolic blood pressure <50 mm Hg in children younger than 12 months; <60 mm Hg in children 1–5 years and <70 mm Hg in children olderthan 5 years of age). Use of additional ASMs. Neurological sequelae at day 180, Day 28 and day 180 mortality. Re-admission to hospital through day 180. Serious adverse events through day 180. Grade 3/4 adverse events through day 180. Length of initial hospitalisation. De-novo evidence of neurological impairments will be ascertained using a modified Kilifi Developmental Index
^
45
^ (which we have adapted to use for the COAST trial)
^
46
^.

Serious adverse events (SAEs) will use the standardized definitions. SAEs will be independently reviewed in real-time by the DMC. Adverse events will be graded following the Common Toxicity Criteria v5.0:

(
https://ctep.cancer.gov/protocoldevelopment/electronic_applications/docs/CTCAE_v5_Quick_Refe rence_5x7.pdf).

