The clinically important adverse events potentially related to the intervention for a Bayesian monitoring approach to be considered by the DMC in this Phase I trial will be an aspiration or respiration depression event (defined as a sudden decrease in oxygen saturations, and/or de-novo coarse chest crepitations, with evidence of gastric reflux/aspirate in the oropharynx). As the Phase II trial comparing levetiracetam to standard of care (control arm) in Malawi had not been reported when this protocol was designed we used the data posted on Trials.gov for the to inform the anticipated event rates. This reported that there were 3/21 events (15%) in the control arm (Trials.gov: NCT01982812). Thus, this has informed a beta prior distribution of (0.23, 1.32) with mean 0.15 (i.e. 15% children experiencing an event) and variance 0.05. We have defined a stopping threshold of 20%, as a previous case series identified very few aspiration events (<1%) in children with acute respiratory failure using the BCV machine
^
35
^. The posterior probability τ was empirically set at 0.95 for the evaluation of this rule
^
47
^. Thus, according to the derived Bayesian decision rule, enrolment will be stopped if the posterior probability of the number of clinically important adverse events being above the target threshold (20%) is higher than 0.95.

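### The bradypnoea cut-offs rise with age while normal respiratory rate falls with age, so the values or the age bands appear transposed

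*Protocol article*

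**What the plan says.** The Safety endpoints section of the protocol article defines the rate criterion in one clause: "bradypnoea defined as <10, 15 or 20 breaths/minute over 3 minutes for those aged <6m, 6–36m and >36m respectively". It belongs to an endpoint worded "Episodes of bradypnoea and hypoxaemia (oxygen saturation <92%) in a child with unrousable coma", with coma taken as a Blantyre score of 2 or less.

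Specific objective (iii), under General objectives, describes the same events differently. It sets out to estimate "episodes of bradypnoea or apnoea; hypoxaemia (oxygen saturations <92" per cent), so apnoea is named and hypoxaemia is a separate item.

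The first inclusion criterion is "Aged 3 months and 12 years (up to 40 kg in weight for paediatric dosing of LVT"), so children can fall into all three age bands. Under Secondary endpoints, feasibility depends partly on whether BCV "averts respiratory safety endpoints".

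**The concern.** A limit for abnormally slow breathing should follow the normal rate, which is highest in infants and falls through childhood. The stated limits go the other way. Hypotension, defined in the same section, also has limits that rise with age (50, 60 and 70 mm Hg). That order suits blood pressure but not breathing rate.

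The Abstract names severe hypoventilation and respiratory arrest as the terminal events, and BCV is in the trial to support breathing through them. A rate criterion that is too low for the youngest children and relatively high for the oldest misclassifies, in a way that depends on age, one of the events the trial sets out to count. The trial is described as active, so if the CRF carries the same order, events are being scored by it now.

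**Working it through.** No sample-size or error-rate formula applies. The check is to read the definition literally and apply it.

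**Step 1: match values to bands.** The word closing the clause in Safety endpoints fixes the pairing in order.

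| Age band | Bradypnoeic if rate is below | 10–14/min | 15–19/min |
|---|---|---|---|
| under 6 months | 10/min | not met | not met |
| 6–36 months | 15/min | met | not met |
| over 36 months | 20/min | met | met |

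The ratio of oldest to youngest limit is 20/10 = 2. No other section gives different limits or explains the order.

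**Step 2: apply it to two children.** A 4-month-old at 12/min does not meet the criterion, because 12 is not below 10. A 10-year-old at 18/min does, because 18 is below 20. Across the whole range 10–19/min the oldest band meets the criterion and the youngest does not.

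**Step 3: add the rest of the endpoint.** As worded under Safety endpoints, an episode also needs saturation below 92% and a Blantyre score of 2 or less.
- The 4-month-old at 12/min, comatose and hypoxaemic, gives no episode.
- The 10-year-old at 18/min, comatose and hypoxaemic, gives an episode.
- The same 10-year-old with normal saturation gives none.

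If bradypnoea and hypoxaemia were instead scored separately, as objective (iii) lists them, the infant would still not be counted as bradypnoeic. The miss in infants therefore holds on either reading. The size of the over-count in older children depends on which reading applies.

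**Step 4: how wide the bands are.** Taking 12 years as 144 months, the enrolled span is 144 − 3 = 141 months.
- Under 6 months: 6 − 3 = 3 months, 3/141 = 2.1%.
- 6–36 months: 30 months, 30/141 = 21.3%.
- Over 36 months: 144 − 36 = 108 months, 108/141 = 76.6%.

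These are shares of the age span, not of children. The article gives no age distribution.

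**Step 5: trace where the limits are used.**
- Safety endpoint on bradypnoea and hypoxaemia: used directly.
- Feasibility (Secondary endpoints): used through the phrase on averting respiratory safety endpoints.
- Hypercarbia (pCO2 above 45 mmHg): a separate safety endpoint with no age bands; not used.
- Bayesian stopping rule (Interim reviews): its event is "an aspiration or respiration depression event (defined as a sudden decrease in oxygen saturations, and/or de-novo coarse chest crepitations", with evidence of reflux; no rate limit, so not used.
- Dose escalation (Sample size determination; Interim reviews): turns on whether 80% need no additional ASM; not used.

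**Step 6: compare objective and endpoint.** Objective (iii) names apnoea and keeps hypoxaemia apart. The endpoint does not name apnoea and joins bradypnoea to hypoxaemia. Absence of breathing throughout the 3-minute window would fall below every limit, so what goes unnamed is shorter apnoea.

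**The case against.** The best defence accepts that the order is wrong and disputes how much follows. Most of its limits stand.

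- A reader might infer that the trial's only measure of hypoventilation is compromised. It is not. Hypercarbia is a separate safety endpoint, monitored by capnography with venous gas verification (Clinical management). The bradypnoea item is the only one based on breathing rate.
- A reader might infer that ordinary rates in older children are scored as events wholesale. As worded, the endpoint also requires hypoxaemia and coma, so a well-saturated older child is not an event. Over-counting is confined to hypoxaemic, comatose children.
- A reader might infer that stopping or dose decisions are affected. Neither rule refers to respiratory rate.
- A reader might infer that the three cohorts could differ spuriously through age mix. The counts could shift, but the Statistical analysis section plans descriptive summaries and no test between cohorts, so no planned inference is distorted.
- The youngest band covers only three months of the enrolled age range, and few children may fall in it.

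The order may also be a slip confined to the article. The documents cannot settle that, which is a reason to check rather than to leave it. None of these points makes the stated definition correct.

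**Conclusion.** The definition is wrong as written and needs correcting. The limits rise from 10 to 20/min across the age bands, the reverse of the age pattern of normal breathing. An infant aged 3 to under 6 months at 10–19/min is never classed as bradypnoeic, while a hypoxaemic, comatose child over 36 months at the same rate is.

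The consequence falls on the one rate-based respiratory safety endpoint and on the feasibility judgement that draws on it. That matters in a trial which states "This is a Phase I trial designed to test the feasibility, tolerability and safety of using non-invasive ventilatory support in cerebral malaria". The mismatch between objective (iii) and the endpoint is real but secondary.

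Two assumptions carry the conclusion. One is that normal respiratory rate falls with age, which is general physiology and not stated in the article. The other is that the published clause reflects what is being scored. The number of misclassified episodes cannot be estimated from the documents.

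**What to change.** 1. Check the three cut-offs and the three age bands against the full protocol, the CRF and the operations manual, and correct their order. No replacement values are proposed here; they should come from the source.
2. Reconcile the safety endpoint with objective (iii). State whether an episode needs both bradypnoea and hypoxaemia or whether they are counted separately, and say how apnoea is recorded.
3. If the CRF carries the same order, re-derive events for children already enrolled where the recorded rates allow. The article mentions a bedside monitor and scheduled assessments (Clinical assessment, Table 1), but does not show that stored rates are dense enough to apply a 3-minute criterion. Where they are not, report that limitation.

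The cost is a short correction to the protocol and, if needed, the CRF. Re-derivation adds work only if the order was carried into data collection. Sample size, the stopping rule and the dose-escalation rule need no change on this account.

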### Interim reviews

The Data Monitoring Committee (DMC) will review data from the first 10 children enrolled to receive LVT. If the DMC consider that it reduces seizures that are short lived and not clinically-relevant i.e. that 80% do not require addition ASMs then an additional 10 children will be studied using LVT at this dosage. If it fails to adequately control seizures, the neuroprotective strategy of BCV plus LVT for those in coma a higher dose (150%) will be studied, namely a 60 mg/kg loading dose followed by 45mg/kg every 12 hours given via nasogastric tube for 3 days or until coma resolution. In addition to assessing whether or not the 150% higher LVT dose should be tested, the DMC will also review the accumulating safety data after each adverse event potentially related to the intervention (as defined below) occurs, using a Bayesian continuous monitoring approach for safety. The Bayesian approach uses information from other studies to define a prior distribution for an expected rate of an adverse event before the trial starts, thus formally inferring available knowledge on safety on children with cerebral malaria in these settings. After each child completes 72 hours from enrolment, they will be defined as having had a clinically important adverse event potentially related to the intervention or not. This information is used to iteratively update the prior distribution and to estimate a posterior distribution. The posterior distribution is then used to estimate the probability of the clinically important adverse event rate being higher than a defined threshold and is continually updated throughout the trial. If the probability reaches a specific pre-defined value, then the DMC is prompted to consider stopping the trial. Thus, the decision rule to be used by the DMC to consider stopping the trial is based on a high posterior probability (τ) that the estimated percentage of children with clinically important adverse events is above a threshold R (equivalently: Pr(P
_events_>R | data)>τ). Thus, this way of monitoring uses both available knowledge from previous studies and accruing data from the ongoing trial to inform decisions.

The clinically important adverse events potentially related to the intervention for a Bayesian monitoring approach to be considered by the DMC in this Phase I trial will be an aspiration or respiration depression event (defined as a sudden decrease in oxygen saturations, and/or de-novo coarse chest crepitations, with evidence of gastric reflux/aspirate in the oropharynx). As the Phase II trial comparing levetiracetam to standard of care (control arm) in Malawi had not been reported when this protocol was designed we used the data posted on Trials.gov for the to inform the anticipated event rates. This reported that there were 3/21 events (15%) in the control arm (Trials.gov: NCT01982812). Thus, this has informed a beta prior distribution of (0.23, 1.32) with mean 0.15 (i.e. 15% children experiencing an event) and variance 0.05. We have defined a stopping threshold of 20%, as a previous case series identified very few aspiration events (<1%) in children with acute respiratory failure using the BCV machine
^
35
^. The posterior probability τ was empirically set at 0.95 for the evaluation of this rule
^
47
^. Thus, according to the derived Bayesian decision rule, enrolment will be stopped if the posterior probability of the number of clinically important adverse events being above the target threshold (20%) is higher than 0.95.

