### Management of cerebral malaria

Quinine was previously the mainstay of treatment for African children with severe malaria for decades; it remains effective and little drug resistance has been reported on the African continent. It has now been replaced by artesunate as the first line antimalarial for severe malaria following findings of the AQUAMAT trial
^
1
^. The AQUAMAT trial conducted in 11 centres in 9 countries in Africa compared quinine and artesunate in 5425 children hospitalised with severe malaria. In the intention-to-treat analysis the primary endpoint, in-hospital mortality, was 297/2713 (10.9%) in those receiving quinine treatment compared to 230/2712 (8.5%) in children receiving artesunate - a relative reduction in mortality of 22.5% (95% CI 8.1-36.9); p=0.002
^
1
^. The sub-group with the greatest mortality were children with coma (cerebral malaria; 33.6% of all participants). Overall mortality in the group with coma was 359/1825 (19.6%)
^
1
^ but this was not substantially better in the artesunate-treated children (18%) than quinine-treated children (21%).

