Two key complications were considered as potential targets for future invention trials. The first was the most common terminal clinic event: respiratory depression and arrest. The second was repeated generalised tonic-clonic seizures which often precipitate the agonal event due to ‘spikes’ in intracranial pressure.

In the absence of mechanical ventilation there are very few options. High Flow nasal therapy and Continuous Positive Airway Pressure (CPAP) devices which apply positive pressure throughout the entire respiratory cycle in patients breathing spontaneously. However, for patients in whose respiratory efforts are compromised BCV applies both negative and positive pressure to the chest, covering both inspiration and expiration phases of breathing, which is more appropriate for periods of hypoventilation and apnoea. Moreover, the BCV is a NIV system that is portable, requires no intubation, does not require specialist medical personnel, and can be used across a wide weight and age range. BCV could be transferred to Africa if studies showed that it could be safely and effectively implemented.

The group consider the currently available ASMs for seizure prophylaxis and chose levetiracetam owing to its favourable pharmacological properties and good safety record – with minimal adverse events relating to respiratory depression. Seizure prophylaxis was considered for all children who have neurological presentations including those with a history of seizures since further seizures are harmful and risk the development of coma and difficulty in breathing. We therefore have modified the original proposal (see protocol versions section) to extend it to those with seizures and prostration (inability to sit upright without assistance in children over 8 months). Respiratory support with combined BCV and seizure prophylaxis was considered only relevant to those with coma.

In summary, to address a therapeutic gap in the management of cerebral malaria, we will explore the potential benefits of negative pressure ventilation (NPV) in combination with levetiracetam as a prophylactic ASM for preventing respiratory arrest and/or preventing or reducing intracranial hypertension by targeting the cerebral vasodilation, as a promising strategy to avert deaths and neurological impairments in children with cerebral malaria. We will also explore levetiracetam as a prophylactic ASM in children who are admitted with seizures in this illness.

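### The Bayesian safety rule scores a child only once 72 hours are completed, so a child who dies or leaves earlier has no defined score, and this does not fit the event-triggered review described beside it

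*Protocol article*

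**What the plan says.** All of this stands in the protocol article under Interim reviews, unless noted.

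- **Scoring time.** "After each child completes 72 hours from enrolment, they will be defined as having had a clinically important adverse event" or not. That result then updates the prior to give the posterior.
- **Review time.** "the DMC will also review the accumulating safety data after each adverse event potentially related to the intervention (as defined below) occurs". The same Bayesian monitoring approach applies there.
- **Counted event.** It is "an aspiration or respiration depression event (defined as a sudden decrease in oxygen saturations, and/or de-novo coarse chest crepitations", and signs of reflux or aspirate are also required. Death is not part of the definition.
- **Prior.** "this has informed a beta prior distribution of (0.23, 1.32) with mean 0.15 (i.e. 15% children experiencing an event) and variance 0.05".
- **Decision.** The cut-off τ is set at 0.95, and "enrolment will be stopped if the posterior probability of the number of clinically important adverse events being above the target threshold (20%) is higher than" that value.
- **Other sight of deaths.** Under Safety endpoints, the DMC reviews serious adverse events independently and in real time.
- **Early death elsewhere.** Under Statistical analysis, a child who dies without recovering from coma is given 36 hours for the primary endpoint. No matching convention is given for the safety rule.

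**The concern.** The rule is specified in full (prior, threshold, cut-off, moment of update), so the moment of update has to work for every child. It does not work for a child who never reaches 72 hours. It also sits badly beside the event-triggered review: an aspiration at hour 10 would bring the DMC to the data, yet under the scoring sentence that child contributes nothing for another 72 − 10 = 62 hours, and perhaps never if the child dies.

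The children affected may not be a random subset. Under Management of cerebral malaria, mortality in comatose children is given as 18% with artesunate. The Discussion, listing two key complications, says "The first was the most common terminal clinic event: respiratory depression and arrest". The account of the Kenyan phenobarbitone trial gives respiratory arrest as the main mode of death in the treated group. If early deaths often follow a counted event, leaving them out removes events from the article's only quantitative safety stopping rule.

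**Working it through.** **Inputs from the article:** prior Beta(0.23, 1.32), threshold R = 20%, cut-off τ = 0.95, 30 children.

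**Inputs the article does not give, so assumed over a range:** m, the share of children who die before 72 hours; q, the chance that such a child had a counted event; r, the event chance in all other children. The 18% mortality is for the whole hospital stay, so it is only an upper guide to m.

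**1. The stated prior reproduces.** Mean = 0.23/(0.23 + 1.32) = 0.148. Variance = 0.23 × 1.32/(1.55² × 2.55) = 0.0496. These match the stated 0.15 and 0.05.

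**2. Stopping boundary.** After k events in n scored children the posterior is Beta(0.23 + k, 1.32 + n − k). The rule fires when Pr(P > 0.20) > 0.95. The smallest k that fires includes 2 of 2, 4 of 7, 5 of 10, 8 of 20 and 11 of 30.

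**3. One unscored child, with no assumption about mortality.** This takes the check at 10 children, with no earlier crossing:

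- All ten scored, 5/10: 0.970, stop.
- One event child died early and is unscored, 4/9: 0.922, continue.
- Two such children unscored, 3/8: 0.815, continue.

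**4. Direction of the bias.** With every child scored, the event rate is p = mq + (1 − m)r. With early deaths unscored, the rule sees only r. The difference is p − r = m(q − r). The literal reading therefore hides events only if early deaths carry the counted event more often than other children do.

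**5. Chance of firing at some point in 30 children.** This is an exact recursion, checked after each scored child. Under the literal reading a child is unscored with probability m, an event with (1 − m)r, and a non-event with (1 − m)(1 − r).

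| m | q | r | true rate p | all scored | early deaths unscored |
|---|---|---|---|---|---|
| 5% | 50% | 25% | 26.25% | 35% | 29% |
| 9% | 50% | 30% | 31.8% | 58% | 48% |
| 9% | 75% | 15% | 20.4% | 15% | 5% |
| 18% | 75% | 15% | 25.8% | 33% | 5% |
| 18% | 30% | 30% | 30% | 50% | 45% |
| 18% | 0% | 30% | 24.6% | 29% | 45% |

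The fifth row has q = r, so its loss comes only from having fewer scored children. The last row shows the reversal.

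**6. True rate held above the threshold.** At p = 30% the rule fires with probability 50.4% if all are scored. With m = 5% unscored this becomes 49.1% (q as in other children) to 34.3% (q = 100%). With m = 18% it becomes 44.7% (q as in others), 28.8% (q = 50%), 13.5% (q = 75%) or 4.8% (q = 100%). At p = 50% the figure is 98.1%, and with m = 18% it falls no lower than 76.2%.

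**The case against.** The strongest reply is that 72 hours is an observation window, after which a child without an event can safely be called a non-event. On that reading an earlier event counts when it happens. The event-triggered review, the description of a continually updated posterior, the target stated as a percentage of children, and the intention-to-treat statement all point that way. This has force: nowhere does the article say that early deaths are excluded. But the only sentence that says when a child's result is assigned says something else, and none of the others says how an early death is scored.

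The second reply is that the DMC sees deaths anyway through real-time review of serious adverse events, and that one sentence makes the rule a prompt to consider stopping. This stands and lowers the severity. It does not settle what enters the posterior, and the closing sentence of the section says that enrolment will be stopped when the posterior crosses.

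The third is that the rule counts aspiration or respiratory depression, with signs of reflux or aspirate, and not death. This also stands. A respiratory arrest without those signs may not qualify, so the terminal-event statement in the Discussion does not give a value for q.

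The fourth is that such conventions belong in a DMC charter or analysis plan. That would answer a mere omission, but here the article itself fixes the scoring time and gives a second timing beside it.

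A reader might infer three stronger things. One is that the rule loses most of its chance of firing. At true rates of 30% or more, more than half is lost only with about 10% early deaths all carrying the event, or about 18% with roughly three quarters or more carrying it. The second is that the bias always favours continuing; step 4 shows that it need not. The third is that children with a recorded event would be recoded as non-events on death; nothing in the article supports that.

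**Conclusion.** The point holds as a badly fixed scoring time. Taken literally, the rule has no result for a child who dies or is withdrawn before 72 hours and delays every event to that time, and this conflicts with the event-triggered review. One unscored event death is enough to turn a stop into a continue at ten children; that result uses only the stated prior, threshold and cut-off. The loss over the whole trial cannot be fixed from the article, because neither the share of deaths before 72 hours nor the event share among them is given. Severity is moderate: the gap is in the only quantitative safety stopping rule, but the DMC has a separate, immediate view of serious events.

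**What to change.** Replace the scoring sentence under Interim reviews with wording to this effect: each child is scored at the earliest of first qualifying event, death, withdrawal or 72 hours from enrolment. A child who dies or leaves before 72 hours is always included, as an event if a qualifying event had occurred by then and otherwise as a non-event. Add that the event-triggered DMC review uses the posterior updated in this way, so that the two timings agree. Optionally, show the DMC a sensitivity posterior with all deaths before 72 hours counted as events.

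For withdrawals, the sentence must also fit the consent provisions. Study procedures says that no data are used if consent is later withdrawn, while Protocol treatment discontinuation says that data already collected are kept, including after assent. These two need reconciling.

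The cost is a sentence or two in the protocol and DMC charter, with no extra data or patients. The prior, threshold and cut-off stay as they are. Where early deaths carry the event more often than other children, the rule will cross somewhat more often than under the literal reading.
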